### 9.2.1 Treatment Assignment Procedures

#### *Randomization of study sites*

We have chosen a cluster-randomized design at the clinic level to avoid contamination that might occur if individual providers in close proximity are randomized to different interventions. Providers who practice at multiple clinics are assigned to the intervention of the clinic for which they spend at least 85% of their time.

Geographically distinct individual clinics will be treated as the unit of randomization. These are clinics belonging to one of three larger clinical organizations covering a connected

geographic area in either Massachusetts (Partners Healthcare consisting of Brigham and Women's Hospital and Massachusetts General Hospital affiliated primary care practices) or Southern California (AltaMed; The Children's Clinic). We will carry out a block randomization of clinics by clinic organization using the statistical computing language R. We first will construct two matrices that each represent a main effects design and together represented the full factorial design ( $2 \times 2 \times 2$  design). For each clinic organization, we will construct ordered collections of clinics. We then will employ the sample function in R to return a random permutation of each ordered collection. For each collection of clinic organizations we will draw a sample that represents the largest number of clinics within each clinic organization that was divisible by 8, the number of study arms. We then will use the list function, a function that ties together related data that do not share the same structure, to assign each randomly permuted clinic to a study arm, repeating this process until clinics have filled the eight arms of the study in equal measure. Because the number of clinics at each organization is not always divisible by eight, we will treat "remainder" clinics across all organizations differently. These remainder clinics will be randomized to conditions within one of the fractional factorial main effects design (a subset of the larger  $2 \times 2 \times 2$  design) to maximize power for main effects estimates. This will be accomplished in a procedure similar to the one described above. One of the two possible fractional factorial designs of the larger  $2 \times 2 \times 2$  design will be chosen randomly to assign remainder clinics to a condition so that remainder clinics have an ex ante equal probability of assignment to any one of the eight conditions in the full factorial design. Allocation of the sequence will be concealed until after the interventions were assigned.

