#### **Sample Size and Population**

We will recruit physicians and advance practice nurses from 49 primary care clinics affiliated with three healthcare organizations who see acute respiratory infection patients. Approximately 300 eligible providers seeing acute respiratory patients will be recruited for this study.

We will randomize practices (blocking on geographical region) to 0, 1, 2, or 3 interventions in a 2x2x2 factorial design to avoid contamination between individual clinicians within the same practice.

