## 9.2 Sample Size and Randomization

Using the correction for inter-cluster correlation from Kish, we estimated the power of our study to detect a clinically significant difference between binary conditions. That is, the sample size must be inflated by a factor of  $1 + \theta(m-1)$ , where  $\theta$  is the inter class correlation and  $m$  is the number of ARI observations per cluster. In our calculations we assumed an intra-clinic correlation of 0.05 and assumed a baseline antibiotic prescribing rate of 50%, an ARI visit rate of 15 visits per month for full time providers, and independence of treatments in the factorial design. We calculated the number of visits needed for an 80% chance (1 – Type II error) to detect a clinically meaningful difference in antibiotic prescribing (7%). We assumed Type I alpha is equal to 0.05, a 75% recruitment success rate for recruiting 376 eligible providers across 49 sites, resulting in 141 providers per study factor (282 clinicians total) and a one-sided  $\alpha$  of 0.05. To achieve statistical power of 0.80 would require a total of 2,252 visits at each factor level, or 4,504 visits across all study conditions. Therefore, if each provider had a minimum of 16 antibiotic-inappropriate ARI visits over the course of the study, we would have sufficient power to detect a clinically significant effect. Randomization is described next in Section 9.2.1.

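### Sending all remainder clinics to one half-fraction partly aliases each intervention with the interaction of the other two, while alternating both halves gives the same main-effect precision

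*Protocol*

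**What the plan says.** The Précis (Sample Size and Population) recruits clinicians "from 49 primary care clinics affiliated with three healthcare organizations", and section 9.2.1 makes the clinic the unit of randomization.

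Within each organisation the full 2x2x2 design is filled using "the largest number of clinics within each clinic organization that was divisible by 8, the number of study arms". The clinics left over are treated differently: "These remainder clinics will be randomized to conditions within one of the fractional factorial main effects design", and the reason given is "to maximize power for main effects estimates". The half-fraction is picked at random so that "remainder clinics have an ex ante equal probability of assignment to any one of the eight conditions in the full factorial design".

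The power calculation in section 9.2 assumes "independence of treatments in the factorial design". Section 9.5 describes a model that estimates each intervention's effect while adjusting for the others. The only interaction it names is time by intervention. The number of clinics per organisation is not stated.

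**The concern.** In either half of a 2x2x2 design, each factor's column is, up to sign, the product of the other two columns. Remainder clinics alone therefore cannot tell the effect of one intervention from the interaction of the other two. If the analysis model has no two-way interaction terms, part of any such interaction enters the estimated main effect, and the model-based standard error does not show it. If the terms are included, the shift disappears but the main effects lose precision.

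Interaction is plausible here. Accountable Justification and Suggested Alternatives are both EHR prompts on ARI visits, and all three interventions act on the same prescribing decision. The question is whether main-effect power requires accepting this exposure.

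**Working it through.** **Plan's own figures.** The protocol gives no figure for the remainder rule. Its only main-effect power figure is the requirement of 2,252 visits per factor level in section 9.2, which does not depend on that rule. The 282 clinicians and 16 visits each reproduce (0.75 × 376 = 282; 4,504/282 = 15.97). The 2,252 does not follow from the stated inputs, but that is a separate matter with no bearing here.

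**Inputs.** 49 clinics, three organisations and eight conditions (Précis, sections 9.2 and 9.2.1). Target difference of 7 points, 80% power, one-sided 0.05 (section 9.2).

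**Number of remainder clinics, r.** Each organisation leaves 0 to 7 clinics, so r is at most 21. Since 49 = 6 × 8 + 1, r must leave 1 on division by 8. Hence r = 1, 9 or 17, and 48, 40 or 32 clinics fill the full factorial.

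**Alias over the whole trial.** Use −1/+1 coding with factors A, B, C. The mean of the product ABC is zero over the full-factorial clinics and ±1 over the remainder.
- One half: r/49 = 1/49 = 0.02, 9/49 = 0.18 or 17/49 = 0.35.
- Both halves alternating in blocks of four: the blocks cancel in pairs (4 − 4 + 1 for r = 9; 4 − 4 + 4 − 4 + 1 for r = 17), leaving 1/49 = 0.02 in every case.

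**Main-effect precision, no two-way terms.** Under either scheme 48 clinics are balanced for main effects and one is odd, so X'X = 48I + xx', where x has four entries of ±1. The variance of a main effect relative to a perfectly orthogonal design is (49/48)(1 − 1/52) = 1.0012. It is the same for one half and for both halves, at r = 1, 9 and 17.

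**Main-effect precision, two-way terms fitted.**
- Both halves: (49/48)(1 − 1/55) = 1.002.
- One half: on the 48 balanced clinics, A and BC have cross-product r − 1, so their sum and difference carry information 48 ± (r − 1). For r = 9, ½(49/56 + 49/40) = 1.050, and the odd clinic brings this to 1.036. For r = 17, ½(49/64 + 49/32) = 1.148, brought to 1.138.
- Using both halves therefore lowers the variance by 1 − 1.0023/1.0361 = 3% or 1 − 1.0023/1.1377 = 12%.

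**With organisation effects fitted (assumed splits).** Relative main-effect variance, one half against alternating halves: 1.0029 and 1.0029 for sizes 20/20/9; 1.0085 and 1.0085 for 20/23/6; 1.0200 and 1.0207 for 23/23/3. These agree to within simulation error.

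**Illustrative shift.** Assume B and C each lower prescribing by 7 points, alone or together. The cell values are 0, −7, −7, −7, so the BC coefficient is (0 + 7 + 7 − 7)/4 = 1.75. The effect of A is twice its coefficient, so without two-way terms it shifts by 2 × 1.75 × r/49:

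| Remainder clinics | One half | Both halves |
|---|---|---|
| 1 | ±0.07 | ±0.07 |
| 9 | ±0.64 | ±0.07 |
| 17 | ±1.21 | ±0.07 |

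**Against the planned precision.** The target implies a standard error of 7/(1.645 + 0.842) = 2.8 points, so the one-half shifts are 0.23 (r = 9) and 0.43 (r = 17) standard errors. For a null third intervention, the one-sided 5% error becomes 7.8% or 11.2% if the shift is favourable, and 3.1% or 1.9% if it is not.

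**The case against.** The strongest defence is that the stated rationale is true. One half-fraction does reach maximal main-effect precision. It beats simple random allocation over eight cells (1.011 for 9 clinics, 1.021 for 17). With organisation fitted it also beats plain permuted blocks of eight (1.0029 against 1.0077 for 20/20/9; 1.0085 against 1.0186 for 20/23/6). A reader might infer that the power claim is false. It is not: the protocol says its choice maximises power, not that no other scheme does as well. What stands against the rule is only that alternating halves match it.

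The harm also needs an interaction that section 9.2 assumes absent, and the full-overlap scenario is an assumption of this review. Even then the shift is under half a standard error. The random choice of half makes its sign symmetric before allocation, so this is not a systematic bias in one direction. That stands, although the trial will be analysed with the one half that was drawn.

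Section 9.5 names no two-way interactions, but whether they are fitted may be settled in an analysis plan that is not at hand. No fault is alleged there, and both cases are shown above.

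A reader might also infer that a small organisation gets no blocking at all, because remainders are taken across organisations. The protocol says the remainder allocation follows a procedure similar to the main one, which runs organisation by organisation. The text is open to either reading, so the point is not made.

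**Conclusion.** The point holds as a design refinement. A reader might go further and say that each intervention is confounded with an interaction in this trial. The documents do not support that: aliasing is complete only among remainder clinics, and with 32 to 48 clinics in the full factorial all main effects and two-way interactions remain separately estimable.

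The trial-wide alias is at most 0.35, and with one remainder clinic there is no consequence. The cost is either a shift whose sign depends on the half drawn (if interventions interact and two-way terms are omitted) or the extra variance computed above (if the terms are fitted). The figures rest on an unstated split of clinics. They weight clinics equally and work on the percentage-point scale, whereas the planned model is a visit-level logistic one.

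Because balanced use of both halves gives up no main-effect precision, nothing is gained by accepting this exposure. Label: free improvement.

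**What to change.** Before randomisation, change the remainder step in section 9.2.1. List the remainder clinics organisation by organisation, in random order within each. Assign them in blocks of four taken alternately from the two half-fractions, with the starting half and the order within each block drawn at random. Every clinic keeps an equal prior chance of each of the eight conditions.

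Reword the rationale to say that balanced use of both halves keeps main-effect precision and limits aliasing with two-way interactions. The cost is a few lines in the R allocation script. After allocation, analysis can remove the aliasing only by fitting the two-way terms at the variance cost shown.

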### **9.3 Interim analyses and Stopping Rules**

No interim analysis will be conducted on primary or secondary outcomes. The Data Safety and Monitoring board is granted the power to recommend discontinuation of the study to each study IRB, if safety concerns are found. The board will meet biannually throughout the duration of the study to review patient safety and adverse events. Following each meeting, the board will make recommendations to the local IRBs as to whether the study should continue or if changes to the protocol are needed. Data for patients who have a return visit to a study clinic within 30 days of an eligible study visit with a diagnosis that could represent a serious complication of an untreated bacterial infection (e.g. acute rheumatic fever, head and neck abscess, intracranial abscess, Lemierre syndrome, mastoiditis, meningitis, pneumonia, sepsis, etc.) will be extracted from study site EHRs and reported to the Board.

### **9.4 Outcomes**

#### **9.4.1 Primary outcome**

The primary outcome is defined as the antibiotic prescribing rate for acute respiratory infection diagnoses changes in antibiotic prescribing rate for the following ICD-9 diagnoses: 460 Acute nasopharyngitis (common cold); 464 acute laryngitis and tracheitis;

465 Acute laryngeopharyngitis/acute upper respiratory infection; 466 Acute bronchitis; 490 Bronchitis not specified as acute or chronic; and 487 Influenza.

#### 9.4.2 Secondary outcomes

To study safety and diagnostic drift we will evaluate an expanded list of potentially appropriate and other diagnoses of interest. For potentially antibiotic appropriate acute respiratory infection diagnoses these are: Acute sinusitis; Acute sinusitis/rhinosinusitis; Acute pharyngitis; 462 Acute pharyngitis. For other acute respiratory infection diagnoses or symptoms of interest these are: Streptococcal sore throat; 034.0 Acute pharyngitis; Cough; and 786.2 Acute bronchitis.

### 9.5 Data Analyses

We will use the following descriptive statistics to characterize the sample: Means and medians for continuous measures, frequencies for count data, standard deviations and interquartile ranges for variance.

For inferential analysis of our hypotheses, we will employ a mixed-effects hierarchical logistic regression model to estimate the adjusted marginal effect over time of each intervention on the primary outcome using. Fixed effects will include intervention assignment, time period dummy variables (the baseline prescribing rate for each clinician, the intervention and intervention months 0-6, 7-12, and 13-18), and time period interacted with intervention assignment. Providers and randomization unit (clinic) will be included as random effects. To isolate the effect of each individual intervention (Suggested Alternatives, Accountable Justification, or Peer Comparison) on the primary outcome, controlling for any co-occurring interventions under the factorial design.

To assess diagnostic drift, we will use the same analytic model as for the primary outcome, but with the percentage of *all* ARIs that is coded as antibiotic-appropriate in each study arm as the dependent variable (a secondary outcome).

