### Design and Outcomes

We will conduct a multi-site cluster randomized trial of 3 behavioral interventions targeting unnecessary antibiotic prescribing during ambulatory visits for acute respiratory infections (ARIs), with practice as the unit of randomization.

The main outcome will be the rate of antibiotic prescribing for ambulatory visits for acute respiratory infections in which antibiotics are inappropriate (i.e., prescribing an antibiotic is inconsistent with published guidelines).

In the main analysis, we will compare a 6-month baseline period to an 18-month intervention period. In subsequent secondary analysis, we will track antibiotic prescribing for another 12 months after the interventions end.

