## **9. STATISTICAL CONSIDERATIONS**

### **9.1 General Design Issues**

#### *Hypotheses*

Our primary hypothesis is that practices randomized to receive behavioral economic interventions will have decreases over time in antibiotic prescribing rates for non-antibiotic appropriate ARIs, compared to contemporaneous antibiotic prescribing rates for non-antibiotic appropriate ARIs among control practices. This hypothesis will be evaluated in an intent-to-treat difference-in-differences framework using a mixed-effects logistic regression model. Fixed effects will include the effects of interventions over time (i.e., interactions between randomization assignment and time), using a 6-months prior to the intervention baseline period. Providers and randomization unit (clinic) will be modeled as random effects.

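### The primary model gives each randomised intervention its own free baseline level; adjusting for baseline instead would save roughly 10 to 20 points of power at the plan's required visit count, and little at higher volumes.

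*Protocol*

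**What the plan says.** Protocol section 9.1 (Hypotheses) sets the framework: "This hypothesis will be evaluated in an intent-to-treat difference-in-differences framework using a mixed-effects logistic regression model". Section 9.5 lists the terms. It says "Fixed effects will include intervention assignment, time period dummy variables" and then, in a bracket describing those dummies, "the baseline prescribing rate for each clinician, the intervention and intervention months 0-6, 7-12, and 13-18", followed by "and time period interacted with intervention assignment". On clustering it adds: "Providers and randomization unit (clinic) will be included as random effects". No clinic-by-period random effect is named.

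The Précis gives the comparison: "we will compare a 6-month baseline period to an 18-month intervention period". The schedule in section 6.1 places baseline prescribing before randomisation on Day 1, and sections 6.2.2 and 9.2.1 make the clinic the unit of randomisation.

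Section 9.2 sizes the trial as a plain comparison of two proportions with a Kish design effect. Its conclusion is that 80% power "would require a total of 2,252 visits at each factor level, or 4,504 visits across all study conditions". It does not model the baseline period or the difference-in-differences contrast.

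**The concern.** With both an intervention main effect and an intervention-by-period term, each factor gets its own baseline level, and the treatment effect is the change from it. Because clinics are randomised, the true baseline differences are zero in expectation. Estimating them subtracts the sampling noise of a short baseline with weight 1. A model with one shared baseline level, or with baseline rate as a covariate, weights the baseline by how well it predicts the later rate.

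What is at stake is precision in every primary comparison, using data that will be collected anyway. Validity is not in question.

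**Working it through.** **Inputs from the Protocol.** Section 9.2: 49 clinics, 282 providers, intra-clinic correlation 0.05, 50% vs 43%, one-sided alpha 0.05, 4,504 visits in total, 15 ARI visits per month for a full-time provider. Précis: 6 and 18 months. Assuming a constant visit rate, there are one third as many baseline as intervention visits.

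**Assumed, because the Protocol does not give it.** r, the correlation of a clinic's underlying rate between baseline and intervention period. The stated random intercepts imply r = 1; I show 1.0 to 0.5.

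**The plan's own figure.** Two proportions, one-sided, 80% power: 627 visits per level before inflation. The inflation formula uses m, which "is the number of ARI observations per cluster"; its value is not given. With m = 4,504/49 = 92 the design effect is 1 + 0.05 × 91 = 5.55, and 627 × 5.55 is about 3,477 per level. The stated 2,252 is therefore not reproduced; it implies m of about 53. I take 4,504 as the plan's stated visit count.

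**Variances of a clinic mean, in units of p(1−p), with all 4,504 visits in the intervention period (92 per clinic, plus 30.6 at baseline).**
- Intervention period: Vpost = 0.05 + 0.95/91.9 = 0.0603
- Baseline: Vpre = 0.05 + 0.95/30.6 = 0.0810
- Difference-in-differences: Vpost + Vpre − 2 × 0.05r
- Baseline-adjusted: Vpost − (0.05r)²/Vpre
- SE = √(4 × 0.465 × 0.535 × V/49); power = Φ(0.07/SE − 1.645)

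At r = 1: difference-in-differences V = 0.0413, SE 0.0290, power 78.0%. Baseline-adjusted V = 0.0295, SE 0.0245, power 88.8%.

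| r | Difference-in-differences | Baseline-adjusted | Loss (points) | Variance ratio |
|---|---|---|---|---|
| 1.0 | 78.0% | 88.8% | 10.8 | 1.40 |
| 0.9 | 70.0% | 83.4% | 13.4 | 1.45 |
| 0.8 | 63.2% | 78.6% | 15.4 | 1.51 |
| 0.7 | 57.7% | 74.7% | 17.0 | 1.58 |
| 0.5 | 49.2% | 69.0% | 19.8 | 1.74 |

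Ignoring the baseline altogether gives 63.9%. Difference-in-differences beats that only if r exceeds Vpre/(2 × 0.05) = 0.81.

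**Other readings, one-sided, r = 1.0 and 0.8.**
- 4,504 visits including baseline: 67.3% vs 82.4% and 55.9% vs 73.9%, losses of 15.1 and 18.0.
- Added provider-level correlation of 0.05 (assumed; generalised least squares on the 2×2×2 layout): losses of 9.0 and 13.7.
- Baseline as long as the intervention period, as the Month −17 to 0 column in section 6.1 would allow: about 1 and 6.
- 15 visits per provider-month (282 × 15 × 18 = 76,140): 0 and 1.9.
- A quarter of that (about 19,000): 0 and 4.7. If r fell to 0.6 the loss there would be about 11.

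**If the shared-baseline model keeps only random intercepts while true r is 0.8.** Its baseline weight is 0.05/0.0810 = 0.617, not the optimum. Then V = 0.0603 + 0.617² × 0.0810 − 2 × 0.617 × 0.04 = 0.0418, and power is about 77.5%, still some 14 points above 63.2%.

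All figures are on the linear-probability scale; the logistic model was not simulated.

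**The case against.** **The visit count is a floor.** Section 9.2 presents 16 visits per provider (282 × 16 = 4,512) as a minimum and assumes 15 ARI visits a month. At that volume the loss almost vanishes. This stands and limits the size of the point. But the 15 a month are all ARI visits of full-time providers, whereas the outcome uses only antibiotic-inappropriate visits after exclusions, and 4,504 is the count on which the plan bases its claim of sufficient power.

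**Baseline may already be adjusted for.** The bracket in section 9.5 names each clinician's baseline rate. It sits among the period dummies, so the reference period is the natural reading, but a covariate cannot be excluded. Section 9.1, for its part, mentions only the interactions. The wording needs settling either way.

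**A free baseline is defensible.** Under section 4.3 the enrolment module tells clinicians their site's assignment, so assignment came before enrolment was complete, and section 5.3 lets clinicians be removed later for diagnostic drift. If enrolment or retention differed by arm, a shared baseline could bias the effect, while difference-in-differences would remove a stable difference. This stands as a reason to keep the unconstrained model as a check.

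**The hypothesis concerns change.** Section 9.1 speaks of decreases over time relative to control. Under randomisation, a baseline-adjusted model estimates the same effect.

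A reader might infer a fixed loss of 15 to 20 points. The documents do not support that: under the stated random intercepts, with the visit denominator of sections 4.1 and 9.1 (intervention period only), it is about 11. The higher figures need a lower assumed r, or a count that includes baseline.

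**Conclusion.** The point holds as one of efficiency. As written in section 9.5, the primary model estimates baseline differences that randomisation makes zero in expectation, and it was less precise than baseline adjustment in every case computed. At 4,504 visits the cost is roughly 10 to 20 points of power across r from 1.0 to 0.5, slightly less with provider-level correlation. The anchor values are 11 points at r = 1 and 15 at r = 0.8. At 4,504 intervention-period visits and r of about 0.8 or lower, the planned contrast is no better than ignoring the baseline; that threshold moves with the visit count. At a quarter or more of the assumed visit rate the cost is 0 to 5 points for r of 1.0 to 0.8.

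It would be wrong to infer that the planned estimator is biased or its test invalid; nothing in the Protocol shows that. The size depends on r, which the Protocol does not give. The change is worth making because it costs little, but the trial's conclusions do not depend on it.

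**What to change.** In section 9.5, make the primary model baseline-adjusted in one of two ways:
- drop the intervention main effects, so that all arms share one baseline level, and keep the period terms, the interactions and the random effects; or
- model intervention-period visits only, with the clinic's baseline prescribing rate as a covariate.

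State whether the clinician's baseline rate in that sentence means the reference period or a covariate; it should not be both. Bring the description in section 9.1 into line. Keep the unconstrained difference-in-differences as a sensitivity analysis.

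The cost is a sentence or two of model wording and no new data. The small downside is that a shared baseline relies on clinician enrolment and retention not differing by arm, which the sensitivity analysis checks.

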### 6.2.2 Enrollment, Baseline, and/or Randomization

#### Enrollment

Enrollment date will be documented on the online consent form at the time of consent. Interventions will be initiated after all clinicians in a practice have been enrolled or declined to participate.

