#### Randomization

We will implement a cluster-randomized design at the clinic level to avoid contamination that might occur if individual providers in close proximity are randomized to different interventions. Providers who practice at multiple clinics will be assigned to the intervention of the clinic for which they spend at least 85% of their time. Geographically distinct individual clinics will be the unit of randomization. We will conduct a block randomization of clinics by clinic organization.

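### Clinics are block-randomised by clinic organisation (the Précis says by region), but the primary model carries neither factor, which costs precision only if prescribing trends differ between organisations

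*Protocol*

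**What the plan says.** Section 6.2.2 (Randomization) states: "We will conduct a block randomization of clinics by clinic organization". Section 9.2.1 repeats it: "We will carry out a block randomization of clinics by clinic organization using the statistical computing language R". It names three organisations, one in Massachusetts and two in Southern California. The Précis (Sample Size and Population) has a different factor: "We will randomize practices (blocking on geographical region) to 0, 1, 2, or 3 interventions in a 2x2x2 factorial design".

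Within each organisation only the largest number of clinics divisible by eight is spread over the eight arms. For the rest, Section 9.2.1 says "we will treat 'remainder' clinics across all organizations differently": they are assigned within a fractional factorial.

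Section 9.5 lists the primary model: "Fixed effects will include intervention assignment, time period dummy variables", then period by assignment, and "Providers and randomization unit (clinic) will be included as random effects". Section 9.1 describes the same model as an intent-to-treat difference-in-differences with a 6-month baseline. Neither list has a term for organisation or region. The diagnostic-drift analysis in 9.5 reuses this model, so it inherits the omission.

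**The concern.** A factor used to restrict the randomisation normally belongs in the analysis. Otherwise the allocation is balanced on it, but the standard error may still be computed as if it were not. The protocol also gives two different names for the factor, so a reader who wanted to add the term could not tell which one is meant.

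A clinic random intercept and a baseline period deal with organisations that prescribe at different constant levels. They do not deal with organisations whose prescribing changes differently over time, and such a change falls on the same time scale as the assignment-by-period effect.

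The protocol gives some reason to expect this. Appendix C describes three EHR systems. In one of them the exclusion logic that suppresses alerts was not implemented, and in the other two it was. Section 7.1 confirms that the Massachusetts and Los Angeles sites count qualifying visits differently with respect to suppressor codes.

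**Working it through.** **The plan's own figure.** The protocol gives no figure for what the blocking is meant to gain. Its only sample-size result, 2,252 visits per factor level (Section 9.2), uses neither organisation nor region. It was not reproduced. The unclustered one-sided requirement for 50% against 43% is 627, so 2,252 implies a design effect of 2,252/627 = 3.59 and m = 1 + 2.59/0.05 = 52.8, but the protocol gives no value for m. That is a separate matter and does not bear on this point.

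**Step 1: level differences.** Write a clinic's baseline as its organisation level plus noise, and its later period as the same level plus the intervention effect plus an organisation-specific change. The level drops out of the difference. Check by generalised least squares with a clinic intercept, four periods, visit variance 0.25 (50% baseline, Section 9.2) and ICC 0.05 (Section 9.2). Assumed: 30 visits per clinic and period before variation in clinic size, and organisations of 22, 21 and 6 clinics.

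| Between-organisation SD (probability scale, assumed) | SE of assignment × period, term omitted | With organisation main effect |
|---|---|---|
| 0 | 0.0350 | 0.0350 |
| 0.05 | 0.0348 | 0.0349 |
| 0.10 | 0.0349 | 0.0350 |
| 0.15 | 0.0348 | 0.0349 |

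Omitting the main effect costs nothing for the primary contrast.

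**Step 2: trend differences.** Simulation of the blocked 2×2×2 allocation of 49 clinics in three organisations, analysing each clinic's change from baseline on the logit scale. Mean model SE with an organisation level SD of 0.5; organisation sizes and SDs are assumed:

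| Organisation sizes | Organisation-by-time SD | Omitted | Included | Ratio |
|---|---|---|---|---|
| 25/22/2 | 0 | 0.139 | 0.140 | 0.99 |
| 25/22/2 | 0.2 | 0.145 | 0.141 | 1.03 |
| 25/22/2 | 0.4 | 0.163 | 0.142 | 1.15 |
| 22/21/6 | 0.2 | 0.147 | 0.141 | 1.04 |
| 22/21/6 | 0.4 | 0.165 | 0.141 | 1.17 |

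In an analysis of change, the organisation term is the organisation-by-period term of the full model. With the terms omitted and SD 0.4, the two-sided 5% test rejected 3.4% (25/22/2) and 3.7% (22/21/6) under no effect. With no organisation differences at all it rejected 6.1% and 5.1%, so one point either way is within simulation noise.

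**Step 3: hand check.** For a main effect over 49 clinics, SE ≈ 2√(σ² + τ²(1 − Σp²))/√49, where τ is the organisation-by-time SD and p the organisation shares. From 0.139 at τ = 0, σ = 0.139 × 7/2 = 0.4865 and σ² = 0.2367. For 25/22/2, 1 − Σp² = 1 − 1,113/2,401 = 0.536.
- τ = 0.2: 2√(0.2367 + 0.0215)/7 = 0.145.
- τ = 0.4: 2√(0.2367 + 0.0858)/7 = 0.162.

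Both agree with the simulation. Near a 50% rate, logit SDs of 0.2 and 0.4 are about 0.25 × 0.2 = 5 and 0.25 × 0.4 = 10 percentage points.

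**Step 4: remainder clinics.** 49 = 6 × 8 + 1. Three remainders of 0 to 7 each must sum to 1, 9 or 17, which is 2%, 18% or 35% of clinics outside complete organisation blocks. Organisation totals are not given, so which of these applies is unknown.

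**The case against.** A protocol's list of fixed effects need not be closed, and stratification covariates are often left to the SAP, which is not at hand. This lowers the weight of the point. It does not remove it, because the protocol sets out the primary model twice without the term and names two different blocking factors.

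Three stronger readings are tempting, and the documents do not support them.

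- *The precision gained by blocking is thrown away.* A reader might infer this by lowering the ICC in the Section 9.2 power formula. That formula concerns variance in clinic level for a simple two-group comparison. The primary effect is assignment by time with a baseline, and Step 1 shows that level differences already cancel. For a post-period-only comparison the loss would be larger (SE 0.177 against 0.145 at a level SD of 0.5, sizes 25/22/2). Section 1.1 and the visit-eligibility rules could suggest such a comparison, but Section 9.1 commits to difference-in-differences.
- *The periods cover different seasons in different organisations.* Section 6.2.2 says "Interventions will be initiated after all clinicians in a practice have been enrolled or declined to participate", which ties the start to the practice, not the organisation. The 5, 7 and 10 months in Appendix C are development and testing times. No start dates are given.
- *A third of clinics are unbalanced on organisation.* 17 of 49 is the upper limit and 1 of 49 is equally compatible with the text. Remainders still go into a balanced fraction by a similar procedure, and imbalance in level is again handled by the baseline.

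**Conclusion.** The point holds in a limited form. Two things are certain from the text: the blocking factor is named inconsistently, and neither version of it is in the primary model. The loss is conditional. If organisations differ only in level, there is none. If their trends differ with an assumed logit SD of 0.2 to 0.4, the SE of assignment by period is about 3% to 15% too wide (4% to 17% with organisation sizes 22/21/6). At the upper end the test is clearly conservative, so the risk is a missed effect rather than a false one.

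The trend SDs and the organisation sizes are assumptions; no figure in the protocol fixes either. The percentages come from a clinic-level analysis of change, whose standard error reflects the observed spread between clinics. The visit-level logistic model with random intercepts only was not simulated, and its standard error may respond less. They are a guide to size, not a prediction. The case for the change is that it matches the analysis to the randomisation at almost no cost.

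**What to change.** In Sections 9.1 and 9.5, add clinic organisation and organisation by period as fixed effects, and carry them into the diagnostic-drift model. An organisation main effect alone does not suffice, because it leaves the assignment-by-period contrast as it was (Step 1). In the Précis, replace geographical region with clinic organisation as the blocking factor, in line with Sections 6.2.2 and 9.2.1.

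The cost is wording in three places and, with three organisations and the four periods of Section 9.5, 2 + 2 × 3 = 8 parameters. No further data are needed, and the SE cost when trends do not differ is 0.140 against 0.139. Organisation by calendar quarter is an optional sensitivity analysis. Over 24 months it needs 2 × 7 = 14 interaction terms, as well as the quarter terms themselves, and may be sparse if one organisation is small.
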